#### Secondary study parameters

Secondary outcomes include the length of hospital stay and duration of operations (including anaesthesia time), complications of surgery and the health-related quality of life (HRQOL) of the operated infants and parental distress and anxiety. Mean (standard deviation, SD) or median (interquartile range, IQR) differences and corresponding 95% CIs will be calculated for length of hospital stay and duration of operations (including anaesthesia time). Odds ratio together with the 95% CI will be calculated for complications. Linear and logistic regression analysis will be performed to adjust for centre and possible confounders (sex, gestational age at birth and initial hernia side). Differences in HRQOL and parental distress and anxiety at baseline before surgery, 4 weeks and 1 year after primary hernia repair and, if relevant, prior to and 4 weeks after re-operation for MCIH will be reported using median and interquartile ranges.

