**Methods:**

The Hernia-Exploration-oR-Not-In-Infants-Analysis (HERNIIA) study is a multicentre randomised controlled trial with an economic evaluation alongside to study the (cost-)effectiveness of contralateral exploration during unilateral hernia repair. Infants aged 6 months or younger who need to undergo primary unilateral hernia repair will be randomised to contralateral exploration or no contralateral exploration (*n* = 378 patients). Primary endpoint is the proportion of infants that need to undergo a second operation related to inguinal hernia within 1 year after primary repair. Secondary endpoints include (a) total duration of operation(s) (including anaesthesia time) and hospital admission(s); (b) complications of anaesthesia and surgery; and (c) participants’ health-related quality of life and distress and anxiety of their families, all assessed within 1 year after primary hernia repair. Statistical testing will be performed two-sided with *α* = .05 and according to the intention-to-treat principle. Logistic regression analysis will be performed adjusted for centre and possible confounders. The economic evaluation will be performed from a societal perspective and all relevant costs will be measured, valued and analysed.

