## Outcomes {12}

### Primary outcome measure

Primary outcome is the proportion of reoperations within 1 year after primary hernia repair. This will be calculated using the number of infants that undergo a second operation related to inguinal hernia repair within 1 year following primary repair, as a fraction of the total number of infants in that group. All participants are seen by a (fellow) paediatric surgeon at the outpatient clinic or via a digital consult 1 year after primary hernia repair. The latter is done to score development of contralateral hernia, testicular atrophy and/or recurrence.

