#### Health-related quality of life (HRQOL) and parental distress and anxiety

HRQOL of the operated infants, parental distress and parental anxiety will be measured by three different validated questionnaires next to the socio-demographic list. HRQOL of the operated infants will be calculated using the TAPQOL (TNO-AZL Preschool Children Quality of Life) [26] scores, with higher scores (range 0–100) indicating better HRQOL. Parental distress and anxiety levels will be calculated using the State-Trait Anxiety Inventory (STAI) [27] and the Distress Thermometer for Parents (DT-P) [28], indicating greater distress and anxiety when revealing higher scores. The questionnaires will be completed by the parents/caretakers at baseline before surgery, 4 weeks and 1 year after primary hernia repair and, if relevant, prior to and 4 weeks after re-operation for MCIH.

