## Statistical methods

### Statistical methods for primary and secondary outcomes {20a}

Data will be assessed using IBM SPSS Statistics Version 25. All statistical testing will be performed two-sided with *α* = .05 and according to the intention-to-treat-principle.

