### Methods in analysis to handle protocol non-adherence and any statistical methods to handle missing data {20c}

Statistical tests will be performed according to an intention-to-treat principle. Efforts will be made in order to reduce missing data to a minimum. Missing data will be imputed using multiple imputation by chained equations. Mixed model analysis will be performed for longitudinal data.

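### The section on secondary parameters names only medians and IQRs for quality of life, distress and anxiety, is not tied to the mixed model in {20c}, and does not mark the re-operation time points as descriptive

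*Protocol article*

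**What the plan says.** All places are in the Protocol article.

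- **Endpoint status.** The abstract's Methods paragraph counts these scores as secondary endpoints: "participants’ health-related quality of life and distress and anxiety of their families, all assessed within 1 year after primary hernia repair".
- **Schedule.** The outcome section on HRQOL and parental distress and anxiety states: "The questionnaires will be completed by the parents/caretakers at baseline before surgery, 4 weeks and 1 year after primary hernia repair". It adds, where relevant, a questionnaire before and one 4 weeks after re-operation for MCIH.
- **Analysis by outcome.** Secondary study parameters gives length of stay and operation time a mean or median difference with a 95% CI, and complications an odds ratio with a 95% CI. It continues: "Linear and logistic regression analysis will be performed to adjust for centre and possible confounders (sex, gestational age at birth and initial hernia side". Only then does it reach the questionnaires, in a sentence that opens: "Differences in HRQOL and parental distress and anxiety at baseline before surgery, 4 weeks and 1 year after primary hernia repair". The same sentence adds the times around a second operation as a conditional item and closes by naming the summary: "prior to and 4 weeks after re-operation for MCIH will be reported using median and interquartile ranges".
- **Longitudinal model.** Section {20c} says: "Mixed model analysis will be performed for longitudinal data". It does not say which outcomes are meant, which contrast is reported or how baseline enters.
- **General principle.** Section {20a}: "All statistical testing will be performed two-sided with *α* = .05 and according to the intention-to-treat-principle".

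**The concern.** Two things need attention.

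First, the section that assigns an analysis to each secondary outcome gives the questionnaire scores a summary and no treatment contrast. Medians and interquartile ranges show how scores are distributed. They give neither an estimated effect of exploration nor an interval around one. Baseline appears as one more time at which differences are shown, although a pre-operative score is most useful as a covariate. The mixed model in {20c} could repair this, but nothing connects it to these scores. Two analysts following the article could reasonably report different things.

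Second, the re-operation time points stand in the same list as the randomised ones. Re-operation is what exploration is meant to prevent: "Primary outcome is the proportion of reoperations within 1 year after primary hernia repair". Under Intervention description, a patent processus or hernia found at exploration is repaired at once. Explored infants who still need surgery for MCIH are therefore a differently selected group from re-operated controls. A gap between arms at those times could be read as an effect of exploration when it partly reflects who was re-operated.

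What is at stake is part of the trial's balance of benefit and burden. The Objectives weigh prevention against the burden of exploration, and the Discussion names questionnaires as one way to assess that burden.

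**Working it through.** **1. The sections side by side**

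| Outcome | Measure named | 95% CI named | Baseline value as covariate |
|---|---|---|---|
| Stay, operation time | mean or median difference | yes | not applicable |
| Complications | odds ratio | yes | not applicable |
| TAPQOL, STAI, DT-P (Secondary study parameters) | median and IQR at each time | no | no; baseline is a reporting time |
| Longitudinal data, not named ({20c}) | mixed model | not stated | not stated |

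The regression sentence lists centre, sex, gestational age and hernia side. Its position suggests that it covers stay, operation time and complications. Even if it also covers the questionnaires, the baseline score is not among its covariates.

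**2. The plan's sample size.** Inputs from Sample size {14} and Sequence generation {16a}: 10% v 2.5%, power 0.80, two-sided alpha 0.05, allocation 1:1.

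- Uncorrected two-proportion formula, with mean proportion 0.0625: n = [1.96 × √(2 × 0.0625 × 0.9375) + 0.8416 × √(0.10 × 0.90 + 0.025 × 0.975)]² / 0.075² = 162.3, so 163 per arm, or 326 in total.
- With continuity correction: (162.3/4) × [1 + √(1 + 4/(162.3 × 0.075))]² = 188.1, so 189 per arm, or 378 in total. This matches the stated figure, so 189 per arm is used below.

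**3. Infants expected at the re-operation times**

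- Control: 189 × 0.10 = 18.9, about 19 (central 95% binomial range 11 to 27).
- Exploration: 189 × 0.025 = 4.7, about 5 (range 1 to 9).

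**4. Precision of an arm comparison there.** For a standardised mean difference, the detectable size at 80% power is (1.96 + 0.8416) × √(1/n₁ + 1/n₂).

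- 19 v 5: 2.8016 × √(1/19 + 1/5) = 1.41 SD.
- 189 v 189: 2.8016 × √(2/189) = 0.29 SD.

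With 19 v 5, power is about 17% for 0.5 SD, 36% for 0.8 SD and 51% for 1.0 SD. Low power is the lesser problem. A larger subset would still be selected by an event after randomisation.

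**5. Gain from baseline adjustment at 4 weeks and 1 year.** Relative to an unadjusted arm comparison, the variance is multiplied by 1 − r², where r is the correlation between baseline and follow-up score. The article gives no r, so a range is assumed.

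| Assumed r | 1 − r² | Variance cut |
|---|---|---|
| 0.3 | 0.91 | 9% |
| 0.5 | 0.75 | 25% |
| 0.7 | 0.51 | 49% |

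**The case against.** **The mixed model.** A reader might infer that the plan yields no baseline-adjusted treatment effect for these scores. The article does not support that. TAPQOL, STAI and DT-P are the obvious repeated clinical measures, so the model in {20c} very probably concerns them, and it can give arm contrasts that account for baseline. Describing scores by medians and also modelling them is compatible. This defence stands: the fault is a missing link between two sections, not a proven absence of an effect estimate. It also limits step 5, since those gains are lost only if the comparison ends up unadjusted.

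**The word differences.** A reader might also infer that the plan prescribes an arm comparison among re-operated infants. The sentence does not say that differences are between arms. Change over time is a possible reading, and the words on relevance echo the collection schedule. The criticism of a non-randomised comparison is therefore conditional. It remains worth making, because these times share a list with the randomised ones and nothing marks them as descriptive.

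**Detail left to the SAP.** Covariates and contrasts for secondary outcomes are often set there, and the SAP is not shown. Silence about model detail would be no finding. Here, however, the article positively names a summary for these outcomes and a different method elsewhere, and that can be reconciled in the text.

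**Other evidence on burden.** Complications, operation time and stay do get estimates with intervals, and quality of life also enters the economic evaluation through EQ-5D-5L. This stands too: the gap concerns the questionnaire scores, not burden as a whole.

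**Means against medians.** The article chose medians, perhaps expecting skewed scores. Keeping them as description meets that. The essential request is one named contrast with an interval.

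**Conclusion.** The point holds as a correction of moderate weight to secondary outcomes. Secondary study parameters names medians and IQRs for these scores, treats baseline as a reporting time and includes the re-operation times. Section {20c} promises a mixed model without tying it to them, and neither section states a treatment contrast with a CI or adjustment for the baseline score.

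If an arm comparison at the re-operation times is intended, it conditions on the trial's own outcome and is not protected by randomisation. It would involve about 19 v 5 infants, with 80% power only for differences near 1.4 SD, against 0.29 SD for the full randomised comparison. These figures assume 189 analysed per arm, the design rates of 10% and 2.5%, complete questionnaires, and re-operations essentially all for MCIH. The 9%, 25% and 49% variance reductions rest on assumed correlations and on an unadjusted comparator. The conclusion does not depend on them. The primary analysis is unaffected.

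**What to change.** Amend the questionnaire sentence in Secondary study parameters, and mirror it in the SAP, along these lines:

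- The arm comparisons of TAPQOL, STAI and DT-P scores at 4 weeks and 1 year come from the mixed model of {20c}. Fixed terms are baseline score, centre, sex, gestational age, initial hernia side, arm, time and arm-by-time.
- Report adjusted mean differences with 95% CIs at 4 weeks and at 1 year. By intention to treat, re-operated infants stay in these comparisons.
- Keep medians and IQRs by arm and time as description.
- Label the questionnaires before and 4 weeks after re-operation as descriptive, with no arm comparison.

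This keeps the protocol's existing covariates and adds the baseline score. The cost is a few lines of wording and a standard model on data already being collected. It changes no visits, questionnaires or sample size.

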#### Economic evaluation

The economic evaluation will be performed from both a societal and healthcare perspective in accordance with the intention-to-treat principle. The economic evaluation will be performed with the number of second operations and quality of life as outcomes. All relevant costs (costs within the healthcare system, costs for patient and family, and costs in other sectors) will be measured, valued and analysed. Healthcare costs are costs of the intervention (unilateral hernia repair with or without contralateral exploration) and costs of treatment of complications. Costs for patient and family include travel expenses, time spending costs and costs of informal care. Costs in other sectors include productivity loss due to work absenteeism by parents/caretakers. We will use a retrospective cost questionnaire and the iMTA Productivity Cost Questionnaire (iPCQ) to measure the direct and indirect costs; 4 weeks and 1 year after primary hernia repair and, if relevant, 4 weeks after re-operation. Costs will be valued using guideline prices recommended in the Netherlands Guideline for economic evaluations in healthcare (Netherlands Health Care Institute, Diemen, 2016)

For estimating quality-adjusted life years (QALY), the patients’ EQ-5D-5L health states (reported by parents/caretakers) will be converted into utility scores using the Dutch tariff [31]. QALYs will subsequently be calculated using linear interpolation between measurement points. Missing data will be imputed using multiple imputation by chained equations [32]. Incremental cost-effectiveness ratio (ICER) will be calculated by dividing the difference in costs by the difference in effects. A cost-effectiveness ratio is calculated to present the incremental costs per re-operation prevented. A cost-utility ratio expresses the incremental costs per QALY. In order to account for the possible clustering of data, analyses will be performed using linear multilevel analyses [33]. Bootstrapping techniques will be used to estimate the uncertainty surrounding the cost-effectiveness estimates. Uncertainty will be shown in cost-effectiveness planes and cost-effectiveness acceptability curves, and sensitivity analyses will be performed to test the robustness of the study results.

## Interim analyses {21b}

No interim analysis will be performed, as this can only be performed after the year follow-up, which will parallel the inclusion of all patients.

### Methods for additional analyses (e.g. subgroup analyses) {20b}

Pre-specified exploratory subgroup analyses will be performed on the primary outcomes stratified by sex (male versus female), gestational age (< 37 versus ≥ 37 weeks), initial hernia side (left versus right) and age at the time of surgery.

Parallel to this RCT, we will perform a qualitative study including a problem analysis for future implementation. We will use the framework of Fleuren et al. to explore facilitators and barriers for implementation of contralateral exploration during unilateral hernia repair on the level of the socio-political context, the organisation, healthcare professionals and the intervention itself [34]. Structured interviews will be held with all relevant stakeholders (e.g. parents, medical professionals, policy makers, patient organisations and health care insurance companies).

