### Who will take informed consent? {26a}

The surgeon explains the study to the parents/caretakers, hands over the information letter and informed consent form, and asks permission to hand over their contact details to the research team. A member of the research team will contact the parents/caretakers to provide more details and answer questions if necessary. As most infants are operated within 3–4 weeks after the outpatient clinic visit, there will be enough time for parents/caretakers to discuss the study and ask any questions before consent needs to be given. At each centre, all (fellow) surgeons who will be involved in this clinical trial will receive training in order to provide information to the parents/caretakers according to the standard operating procedure (SOP) and Good Clinical Practice (GCP) guidelines.

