#### Intervention group: unilateral hernia repair with contralateral exploration

Surgical inguinal hernia repair is done similarly in all patients. An incision is made in the groin. The hernia sac is identified, divided from the vas deferens and testicular vessels (in boys) and cleaned to the level of the internal inguinal ring. It is twisted on itself and ligated at the level of the internal inguinal ring. The skin is closed. Duration of unilateral inguinal hernia repair is approximately 60 min (including anaesthesia time). Exploration of the contralateral side and potential contralateral hernia repair will increase anaesthesia time by approximately 15 min.

Contralateral exploration will be used to identify a PPV or hernia on the other side than the side on which the child has to be operated on. If during contralateral exploration, a hernia or PPV is present, contralateral repair will be performed. This will be exactly the same procedure as the inguinal hernia repair on the symptomatic side. If a hernia or PPV is absent during contralateral exploration, the skin will be closed. There is no need for extension of postoperative hospital admission or addition of other interventions.

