### Concealment mechanism {16b}

Treatment allocation will be concealed by using a web-based application with a computer-generated list with varying block sizes that will not be disclosed and is stratified by centre. Participants and care providers are aware of allocation.

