### Implementation {16c}

After obtaining informed consent, participants will be randomly allocated to one of the two study groups by the researcher using Castor EDC.

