### Procedure for unblinding if needed {17b}

This is an open label trial; therefore, an unblinding procedure does not apply.

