## Data collection and management

### Plans for assessment and collection of outcomes {18a}

Data of participants and findings for primary and secondary outcome measures will be recorded by the (fellow) paediatric surgeon or one of the investigators in a web-based electronic case record form using Castor EDC [30]. Parents/caretakers will use the online KLIK PROM (patient-reported outcome measures) portal (www.hetklikt.nu) to answer questionnaires.

The study will collect the following baseline characteristics and data from the participants: sex, gestational age, birth weight, comorbidities, inguinal hernia in first degree siblings, age and weight at day of surgery, preoperative size of both testes (in boys), side of the inguinal hernia and other hernia characteristics (e.g. preoperative history of hernia incarceration and surgical findings during contralateral exploration (i.e. presence of a PPV or not), total duration of surgery and hospital admission, total number of hospital visits and complications.

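### One exploratory subgroup is defined by age at surgery, a variable fixed after open randomisation; age at randomisation would be a safer choice at no cost (minor)

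*Protocol article*

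**What the plan says.** Under Methods for additional analyses {20b}, the protocol article announces: "Pre-specified exploratory subgroup analyses will be performed on the primary outcomes stratified by sex". Gestational age follows as the second factor, and the list ends with "initial hernia side (left versus right) and age at the time of surgery".

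Four other places bear on the timing of that last variable:

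- Implementation {16c}: "After obtaining informed consent, participants will be randomly allocated to one of the two study groups by the researcher using Castor EDC". The allocation decides which operation is done, so surgery comes after it.
- Concealment mechanism {16b}: "Participants and care providers are aware of allocation". The section on unblinding {17b} confirms it: "This is an open label trial; therefore, an unblinding procedure does not apply".
- Informed consent {26a}: "As most infants are operated within 3–4 weeks after the outpatient clinic visit". The interval from randomisation to surgery is not given, nor is the point at which the operation date is booked.
- Plans for assessment and collection of outcomes {18a}: age on the day of surgery is listed together with baseline characteristics, although it is known only after allocation.

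Date of birth is collected at the baseline assessment (Participant timeline {13}).

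**The concern.** A subgroup comparison keeps the protection of randomisation only if membership is fixed before, or cannot be affected by, the allocation. Sex, gestational age and initial hernia side meet that condition. Age at surgery meets it only if allocation has no influence on when the infant is operated on. In an open trial that is an assumption and not a property of the design.

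If one arm waited longer, some infants in that arm alone would move from the younger to the older stratum. The arms within each stratum would then differ in age composition, and the stratum odds ratios could change although the effect of exploration had not. Age also carries much of the trial's rationale: the Background section gives a 12.4% risk of contralateral hernia under 6 months against 5.8% overall. Readers are therefore likely to look at this subgroup, even though it is labelled exploratory.

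**Working it through.** The plan gives no figure on this point, so what follows is an illustration under stated assumptions.

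**1. Arm size.** Sample size {14} gives 378 infants for 10% versus 2.5%, power 0.80, two-sided alpha 0.05. The two-proportion formula with continuity correction gives 189 per arm, and 2 × 189 = 378, so the figure reproduces. It is used below only as the arm size.

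**2. How many infants could change stratum.** Assume age at randomisation uniform over 26 weeks (182 days) and one cut-point. If one arm waits D days longer, the share of that arm crossing the cut is D/182.

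| Extra wait in one arm | Share crossing | Of 189 infants |
|---|---|---|
| 0 days | 0 | 0 |
| 3 days | 1.6% | about 3 |
| 7 days | 3.8% | about 7 |
| 14 days | 7.7% | about 15 |

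A wait common to both arms (21/182 = 11.5%, 28/182 = 15.4%) moves infants equally in each arm and creates no difference between arms.

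**3. What that does to the stratum odds ratios.** Further assumptions: cut at 13 weeks of age at surgery, control wait 3 weeks, exploration wait 5 weeks, control risk averaging 10% and falling exponentially with age at rate k per week, risk ratio 0.25 throughout. Infants below the cut number 189 × 10/26 = 73 in the control arm and 189 × 8/26 = 58 in the exploration arm.

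If risk depends on age u at randomisation, the risk is c·exp(−k·u), and its mean over ages a to b is c·[exp(−k·a) − exp(−k·b)] / [k·(b − a)]. For k = 0.06:

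- c = 0.10 × 1.56 / (1 − exp(−1.56)) = 0.1975.
- Control: 0.1485 in the younger stratum (u from 0 to 10) and 0.0697 in the older (10 to 26).
- Exploration with equal waits: 0.25 × these = 0.0371 and 0.0174, giving odds ratios 0.221 and 0.237.
- Exploration with a 5-week wait: 0.0392 (u from 0 to 8) and 0.0187 (8 to 26), giving odds ratios 0.234 and 0.254.

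If risk depends instead on age at surgery, the two extra weeks multiply the exploration risks by exp(−0.12) = 0.887. They become 0.0348 and 0.0166, and the odds ratios are 0.207 and 0.225.

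| k per week | Equal waits (younger / older) | 2 weeks longer, risk by age at randomisation | 2 weeks longer, risk by age at surgery |
|---|---|---|---|
| 0.06 | 0.221 / 0.237 | 0.234 / 0.254 | 0.207 / 0.225 |
| 0.10 | 0.215 / 0.240 | 0.235 / 0.273 | 0.191 / 0.223 |

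The same difference in waiting pushes both odds ratios up under one risk model and down under the other.

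**4. Comparison with sampling error.** The largest upward shift is ln(0.273/0.240) = 0.13, and the largest downward shift is ln(0.191/0.215) = −0.12. In a stratum holding half the sample (about 94 per arm, 10% versus 2.5%, so about 9 and 2 expected events), the standard error of the log odds ratio is √(1/9.4 + 1/84.6 + 1/2.35 + 1/91.65) = 0.74. With an extra wait of 3 days, k = 0.06 and risk by age at randomisation, the odds ratios move only from 0.221 and 0.237 to about 0.224 and 0.240.

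**The case against.** The strongest reply is that nothing in the article shows a problem in practice. It does not say when the operation date is fixed relative to allocation. If the slot is booked at the clinic visit, allocation cannot move it. The exploration procedure "will increase anaesthesia time by approximately 15 min", but no section links those minutes to a later date, and the two-week difference used above is an assumption. The subgroup is exploratory, and the adjusted primary model does not include age at surgery. All of this stands, and it limits the weight of the point. It does not make age at surgery a pre-randomisation variable.

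A reader might infer three stronger criticisms, none of which the article supports:

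- **A predictable bias in one direction.** The sign depends on whether risk follows age at randomisation or age at surgery. The article does not settle this; the primary outcome's one-year window starts at the repair (Outcomes {12}), so the second reading is plausible.
- **A missing cut-point for age.** The article refers to a separate statistical analysis plan, which is not shown, and a cut-point for an exploratory subgroup can properly be left to it.
- **A breach of intention to treat because infants never operated on have no stratum.** Such an infant has no age at surgery, and imputation cannot supply an age at an event that did not occur. But the same infant also lacks the starting point of the primary outcome, so the difficulty is not specific to this subgroup. The article gives no number of such infants and does not say that they would be dropped.

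**Conclusion.** The point holds as a minor one. Age at surgery is the only one of the four subgroup factors fixed after randomisation, and allocation is open. Whether stratum membership will differ between arms depends on whether allocation influences the operation date, which the article leaves open. The resulting bias is zero with equal waits and of unknown size and direction otherwise. It is probably small: within about ±0.13 on the log-odds scale under the assumed two-week difference, against a standard error of about 0.74. Those figures rest on uniform ages, a 13-week cut, exponential decline in risk and a constant risk ratio, none of which comes from the article. The primary analysis and the sample size are not affected.

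**What to change.** In Methods for additional analyses {20b}, replace the last item of "initial hernia side (left versus right) and age at the time of surgery" with age at randomisation, calculated as the randomisation date minus the date of birth, for every randomised infant. Keep age at surgery as a descriptive variable, reported by arm; this will also show whether waits differed. Entering age as a continuous variable in a treatment-by-age interaction is optional and would avoid choosing a cut-point.

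The cost is a change of wording in the protocol or the analysis plan. Date of birth is already collected and the randomisation date comes from the web-based allocation, so no new data are needed. The change does not by itself settle how infants without surgery enter the primary outcome.
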